## Abstract

**Background:**

Early sexual initiation is associated with higher risk for sexually transmitted infection, teen pregnancy, domestic violence and substance use in later adolescence and early adulthood. Native American adolescents are more likely to have early sexual initiation compared to other racial/ethnic groups. Few programs designed with and for Native adolescents to delay sexual initiation and substance use have been tested through rigorous evaluations. This is the protocol for the randomized controlled trial of the Asdzáán Be’eena’ program, a teen pregnancy and substance use prevention program for young Native girls and their female caregivers.

**Methods:**

*N* = 410 female adolescents ages 10–14 and their female caregivers will be enrolled in the study and randomized to the intervention or control arm. The intervention consists of the 11-session Asdzáán Be’eena’ program. The control arm consists of mailed non-monetary incentives. All participants will complete evaluations at baseline and 3 follow-up timepoints (immediate, 6 and 12 months post intervention). Evaluations include measures to assess protective factors associated with delayed sexual initiation and substance use.

**Discussion:**

This is one of the first rigorous evaluations of a gender-specific, culturally tailored teen pregnancy and substance use primary prevention program for Native girls and their female caregivers. If proven efficacious, Native communities will have a culturally appropriate program for promoting protective factors associated with delayed substance use and sexual risk taking.

**Trial registration:**

NCT04863729; April 27, 2021.

## Introduction

### Background and rationale

Extensive research documents how both early sexual debut and substance use intiation adversely impact the health of an individual. Specifically, early sexual debut increases the likelihood of poor sexual and reproductive health outcomes, such as sexually transmitted infections (STI) and unintended teen pregnancy [1–4]. It is also associated with a greater number of sexual partners and increased risk of being a victim of intimate partner violence [4–6]. In terms of substance use, early initiation of substance use adversely impacts the cognitive and emotional growth and development of adolecents [7–9].

Early sexual debut and substance use are also costly for the individual, society and tax payer. A recent analysis conducted by Rotz et al. found large economic savings of preventing teen sexual activity and substance use. The analysis estimates a net benefit of up to $52,109 for females and $27,861 for males from delaying voluntary sexual activity to age 15 or older [10]. For substance use, the estimated cost savings for preventing underage drinking is estimated to be up to $12,313 for individuals [10].

Not surprisingly, substance use initiation is one of the most significant risk factors for sexual initiation and unprotected sex among adolescents. In fact, these behaviors tend to co-occur, particularly among more vulnerable subgroups of adolescents [11, 12]. These behaviors also share similar risk factors including lack of family cohesion [13–17] and poor adolescent functioning (having high levels of internalizing and externalizing behaviors). They also share many protective factors including connection to culture [18–21], parent-child relationship, self-efficacy and future aspirations [21–26]. Programs targeting these shared risk and protective factors may have a dual impact: reducing both sexual risk taking and substance use among adolescents.

National data show Native American (Native) adolescents are more likely to initiate sex before age 13 than all other U.S. racial/ethnic groups, except African American adolescents [27]. Native high school youth are also more likely to have multiple sex partners and to ever have had sex compared to youth of all races [27, 28]. Native youth also experience higher rates of STIs and teen pregnancy than their non-Native counterparts; in 2018, U.S. national Chlamydia and Gonohrrea rates among Native Americans were 3.7 and 4.6 times higher than that among Whites [29]. Further, in 2017, the national teen birth rate among 15–19 year old Native Americans was the highest of all races and ethnicities [30, 31]. It follows that Native adolescents have higher rate of substance use and abuse. Compared to all U.S. adolescents, in 2018, Native adolescents ages 12–17 are more likely to engage in past-month binge drinking (5.7% vs. 4.9%), marijuana use (11.1% vs. 7.4%), and other illicit drug use (12.8% vs. 8.7%) [32].

Given the adverse outcomes of early sexual activity and substance use and the high rates of sexual risk taking and substance use among Native adolescents, prevention efforts to delay these behaviors in Native communities are warranted [33]. These efforts may be more advantageous if delivered during early adolescence (ages 10–14), before a child initiates sex or substance use. Early adolescence is a key developmental period in which children continue to solidify their values and relationships, and learn foundational life skills [34–37]. Hindered growth in these areas during this time period has been linked to poorer health outcomes including early sexual initiation, substance use and abuse in later adolescence and adulthood [33]. Thus, programs that promote values, focus on building healthy relationships and teach life skills such as problem-solving and goal-setting in early adolescence are needed.

As opposed to many Western societies, most Native cultures do not have a self-centered orientation to health, but instead have family- and community-oriented health frameworks [38]. Thus, intergenerational programming may be more culturally appropriate [39] than individual-level programs. In addition to cultural congruency, engaging parents alongside adolescents in programming may be advantageous as they can support and reinforce behaviors [40, 41]. While robust efforts have begun to address behavioral health disparities among Native adolescents, currently there are no intergenerational, efficacious primary prevention programs targeting the dual threat of sexual risk taking and substance use for young Native adolesents [42–44]. This study seeks to fill this gap.

### The current study

The objective of the is to assess the efficacy of a program called Asdzáán Be’eena’ (Female Pathways, AB) for increasing protective factors associated with delayed substance use and sexual risk taking among Native girls in early adolescence (ages 10–14) through a randomized controlled trial (RCT). This paper describes the study protocol.

### Objectives

The study will test the efficacy of the AB program on risk and protective factors associated with delaying adolescent substance use and sexual initiation, as well as actual sexual initiation and substance use. By assessing protective and risk factors as well as behaviors among the adolescent and the caregiver, the study team will be able to assess how each of these are impacted by the intervention, and how these interact with one another to moderate program impact.

Primary research questions include: 1) Is the intervention effective in increasing adolescents’ intention to abstain from sex (intention to abstain was chosen as opposed to sexual initiation as we do not anticipate high rates of sexual initiation for the duration of the follow-up time period); 2) Is the intervention effective in improving caregiver-adolescent relationships. Secondary research questions include: 1) Is the intervention effective in improving adolescent risk and protective factors associated with delayed sexual initiation and/or substance use initiation; 2) Is the intervention effective in improving caregiver risk and protective factors associated with delayed adolescent sexual initiation and/or adolescent substance use initiation; 3) Is the intervention effective in delaying sexual initiation and substance use initiation among adolescents; 4) Is the intervention effective in reducing substance use among enrolled caregivers.

The study team hypothesizes a higher proportion of adolescents in the intervention group will state they intend to abstain from sex in the next year and until they graduate high school compared to the control group at 6- and 12-months post intervention. Additionally, we hypothesize that there will be 1) an increase in caregiver-adolescent communication at 6- and 12-months post intervention as measured by a communication scale adapted from a trial with Ojibwe adolescents, 2) an increase in caregiver-adolescent quality time together at 6- and 12-months post intervention as measured by a quality time with parent scale adapted from a trial with Ojibwe adolescents, 3) an increase in maternal warmth at 6- and 12-months post intervention as measured by the Authoritative Parenting Index, and 4) an increase in caregiver monitoring at 6- and 12-months post intervention as measured by the parental monitoring scale.

### Trial design

The study is a two-armed randomized controlled trial examining the primary outcomes of adolescent-caregiver relationship, adolescent intention to have sex and adolescent adaptive/maladaptive functioning at 12 months post intervention. The trial is being conducted at two study sites on the Navajo Nation with Navajo girls ages 10–14 and their female caregiver. Randomization will be performed with a stratified block randomization sequence to ensure a 1:1 allocation of study conditions within each of the two study sites Fig. 1.

**Fig. 1 Fig1:**
[figure not shown]
Trial Design

## Methods/design

### Study setting

The study will be conducted by the Navajo Nation in partnership with Johns Hopkins Center for American Indian Health (Center). The study design was approved by the appropriate Navajo governing bodies including Chapters, Agency Councils and Health Boards as well as the JHU research review board and the Navajo Nation Human Subjects Research Review Board (NNHRRB). This manuscript was approved by the NNHRRB. All deviations from the protocol will be approved by IRBs before being implemented. Once approved, they will be updated in clinicaltrials.gov by the PI. As needed, participants will be reconsenting utilizing consenting documents that include changes to the protocol and have been approved by the appropriate IRBs.

The study is community based intervention and conducted on the Navajo Nation in the United States of America.

#### Study staffing

This study is being conducted at two study sites on the Navajo Nation. The Center has had a physical office and has conducted projects in partnership with the Navajo Nation for over 30 years. Each site has two family health coaches (FHCs), one independent evaluator (IE) and one site coordinator. Other members of the study team, including the principal investigator, program manager, program coordinator and evaluator, are located at the Center’s administrative office in Baltimore, Maryland. The field manager is located in Arizona near the Navajo Nation. All members of the study team are full-time Johns Hopkins employees and are thoroughly trained in human subjects research prior to working with participants. Members of the Baltimore team and the field manager make frequent trips (at least bi-annual) trips to the study sites to conduct training and quality assurance.

#### Family health coaches

FHCs are Navajo women living in one of the study communities. All speak some Navajo. All FHCs will complete extensive (> 60 h) of training in the program curriculum as well as skills necessary to deliver the program including home-visiting, group facilitation, and boundary setting. They will be responsible for delivering the AB program to dyads. They will also be responsible for delivering the non-monetary retention gifts to dyads in the control group.

#### Independent evaluators

Independent Evaluators are Navajo women living in one of the two study communities. All speak some Navajo. All IEs will complete extensive training (> 40 h) in the study protocol including recruitment, consenting and data collection. IEs will recruit participants, administer informed consent, receive parental permission and adolescent assent. IEs will also administer all assessments and provide gift cards for assessment completion.

#### Site coordinators

Site Coordinators are Navajo women living in one of the two study communities. They will provide on-site support to all local study staff.

### Participants and eligibility criteria

Participants are Native female adolescents and their female caregiver (referred to as dyads). Inclusion criteria for the adolescent includes: Native American ethnicity, 10–14 years of age, living within 50 miles of one of the two study sites, and written parental permission and adolescent assent. Participant inclusion criteria for the caregiver includes: Native American ethnicity, ≥ 18 years of age, caregiver to a female child age 10–14 years who will enroll in the study with them, living within 50 miles of a study site, and written informed consent. If the caregiver is not the legal guardian of the adolescent, the adolescent’s legal guardian must agree for the caregiver to participate. To honor cultural views around caregiving, female caregivers who live outside of the home but play a pivotal role in child rearing are welcome to participate. To enroll, both members of the dyad (adolescent and caregiver) must be eligible and enroll. Adolescents in foster care are ineligible to participate.

### Interventions

#### The Asdzaan Be’eena’ program

The AB program is described in detail elsewhere (Chambers 2021). A short description is included here.

#### Program development

Program development occurred from 2016 to 2018 and included the following: 1) 12 focus groups and 15 interviews with Navajo girls ages 8–25, mothers and grandmothers, fathers and grandfathers, as well as traditional practitioners, 2) 10 Community Advisory Board (CAB) meetings each consisting of 8–12 community leaders, 3) administration of a survey to 400 Navajo adult women to assess preferences and experiences with puberty, 4) a three-day intensive workshop with cultural specialists and 5) an extensive review of the literature to identify other programs and requisite risk and protective factors to delay sexual initiation and substance use among Native girls in pre- and early adolescence. Lessons were drafted by the Johns Hopkins curriculum team in consultation with cultural experts, reviewed by the CAB and piloted with *N* = 47 dyads. Evaluation assessments were piloted with participating mothers and daughters at baseline and 3 month time points. Pilot findings indicate the program positively impacted communication between girls and their female caregivers (*p* = 0.2; *p* < .001), improved cultural (*p* = .02) and reproductive health knowledge (*p* = .001), while simultaneously reducing internalizing behaviors (*p =* .001), deviant disorder symptoms (*p* = .04), and attention deficit disorder (*p* = .03) at 3 months post program completion. Female adolescents who completed the program were also more likely to state that they planned to wait to have sex until married (25% vs. 70%, *p* = .218). This preliminary data justified rigorous evaluation of the AB program for impacts on delayed sexual and substance use initiation.

#### Program curriculum

The AB program is a culturally grounded curriculum consisting of eleven lessons organized according to the teachings of the Navajo creation story, designed specifically for Navajo females. Lessons also provide knowledge and skills necessary for delaying substance use and sexual initiation as identified through the focus groups, in-depth interviews and literature review. All lessons are taught by a FHC, and consist of three to five activities designed to teach a skill or provide knowledge about a topic (see table below). At the end of each lesson, 1) the FHC reviews key teachings from the lesson, 2) dyads practice three to five Navajo vocabulary words, 3) the FHC provides the dyad with a positive affirmation, 4) the dyads are given worksheets with information and activities completed during the session, and 5) the FHC gives a scheduling reminder for the next lesson.

#### Program implementation

The AB curriculum is implemented through a mix of individual dyad and group formats (see Table 1). Individual dyad lessons are taught by one FHC to a dyad in their home or another place of their choosing (e.g. the local program office, a local school or clinic). Snacks are provided to dyads during these sessions. Group lessons are taught by 2 FHCs (facilitator and co-facilitator) to groups of 7–12 dyads in a central location in the community (e.g. chapter house, local clinic or school). Meals are provided to dyads during group sessions and transportation to group sessions is provided as needed. Participants complete the program in cohorts of 7–12 dyads. All members of a cohort participate in group lessons together.

**Table 1 Tab1:** AB Lesson Delivery Format and Content

Lesson number	Format	Topic
1	Individual dyad	Program introduction; discussion of the meaning of the clan system; importance of self-reflection in Navajo culture
2	Individual dyad	Identifying role models; respect for self, others and mother earth
3	Group	Building the caregiver adolescent relationship; strategies for improved communication
4	Individual dyad	Developing support networks; Navajo introductions; family roles and values
5	Group	Navajo history, Navajo teachings related to puberty; Introduction to the female reproductive system
6	Individual dyad	Thinking positively; problem solving skills development
7	Group	Communication styles; dealing with peer pressure; refusal skills
8	Individual dyad	Community and family values; support networks; Kinaaldá (Navajo coming of age ceremony) teachings
9	Group	Reproductive Health 101: puberty and pregnancy; healthy hygiene during puberty; skills to improve caregiver-adolescent communication about sensitive topics Caregiver only: safe sex practices
10	Individual dyad	Self-esteem; identifying personal strengths; goal setting skills
11	Group	Holistic health; promoting others; taking lessons learned forward

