#### Control condition

The control condition consists of the delivery of four non-monetary retention items totaling <$20/dyad to the participant’s home. Retention items were selected by the community and provided as a way to continue to stay in contact with families for follow-up data collection.

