### Randomization and sample size

This study will use a 1:1 randomized controlled trial design; the unit of randomization will be the individual dyad. Unique participant identification numbers will be used to randomize individual dyads to one of two study groups: intervention or control. Stratified block randomization, using random block size will be used to ensure a 1:1 allocation of study conditions across the two study sites. The sequence will be generated by the program evaluation via STATA and will not be shared with study staff who enroll participants.. Independent Evaluators will enroll participants and reveal study group after the participants complete the baseline assessment. The study assignments are sequentially numbers in sealed envelopes that are only opened at the time of randomization. No blinding will occur.

Sample size and statistical power estimates are predicated on 2 primary hypotheses: 1) that those randomized to the AB intervention will have improved parent-adolescent communication compared to the control group, and 2), that those randomized to the AB intervention group will have a higher proportion of participants who report they intend to abstain from sex.

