The sample size of 410 dyads (*n* = 205 per study arm) will be sufficient to detect a 0.3 difference between study groups, with 90% power and 0.05 significance level, on the communication scale at 12 months post-intervention (estimating a mean score (SD) of 2.81(0.85) in the control group). This same sample size will be sufficient to detect an 18% between-group difference, with 80% power and 0.05 significance level, in the proportion of participants who report intention to abstain from sex at 12 months post-intervention (estimating 50% of the control group to report intention to abstain from sex at 12 months post-intervention). This sample size will also be able to detect meaningful differences in other key confirmatory research question outcomes at 12 months post-intervention. The following presents minimum detectable differences between the intervention and control groups with at least 80% power, given the assumptions listed above: 0.39 between-group difference in internalizing behaviors (estimating a mean score (SD) of 5.23 (0.99) in the control group), and 0.25 between-group difference in externalizing behaviors (estimating a mean score (SD) of 2.04 (0.63) in the control group). All estimates assume 10% attrition between enrollment and program completion and a 25% attrition rate between program completion and the 12 month follow-up time point.

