### Statistical analysis

The between study group equivalence of participant characteristics and outcome measures at baseline will be compared using Chi-squared tests (dichotomous/categorical data) and t-tests (continuous data). Study hypotheses related to the confirmatory questions will be initially tested under an “intent-to-treat” model in which data are analyzed according to treatment assignment at randomization. We will then conduct “completer analyses” on those subjects completing at least two-thirds of intervention sessions. Intervention impact will be evaluated by comparing primary study outcomes between intervention and control groups across the three time points: baseline, 6 months and 12 months post-intervention. Initially, summary scores of outcomes will be stratified by participation in the intervention versus control groups and by time point, and will be compared using chi-square tests (binary or categorical outcomes), t-tests and analysis of variance (continuous outcomes). Generalized linear mixed effects models (GLMM) accounting for within-group correlation across longitudinal data will then be applied. Outcomes will be modeled as a function of group assignment and time since intervention. The association between outcomes and time will be explored visually using scatterplots and lowess smoothers. Restricted cubic splines will be added to reflect deviations from linearity.

If siblings enter the study, they will be randomized to the same intervention group to limit contamination. In this case, analyses will be adjusted to take into account intra-sibling correlation as well. Additionally, sensitivity analyses will be conducted including and excluding siblings to examine the impact on study results. Missing data will be handled as follows: 1) identify erroneous data, 2) document reason(s) for missing and erroneous data to inform model development; 3) compare demographic characteristics of those who dropped out and those who did not to compare if data is missing at random; and 3) conduct sensitivity analysis to compare inferences that are based on different plausible reasons for missingness. Navajo and Hopkins investigators will collaborate with community partners in data interpretation to assure accuracy, cultural acceptance and relevance.

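### Group delivery to cohorts in the intervention arm only is not reflected in the stated model or sample size; if cohort-mates' outcomes correlate, standard errors are understated and communication power falls below 90%

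*Protocol article*

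**What the plan says.** Randomization is by dyad: "This study will use a 1:1 randomized controlled trial design; the unit of randomization will be the individual dyad" (Randomization and sample size). Delivery in the intervention arm is partly by group: "Participants complete the program in cohorts of 7–12 dyads. All members of a cohort participate in group lessons together" (Program implementation). Table 1 lists lessons 3, 5, 7, 9 and 11 as group lessons and the other six as single-dyad lessons. The control arm has no grouping: "The control condition consists of the delivery of four non-monetary retention items totaling <$20/dyad to the participant’s home" (Control condition).

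Under Statistical analysis, the correlation structure is described twice. For the main model: "Generalized linear mixed effects models (GLMM) accounting for within-group correlation across longitudinal data will then be applied", with study group and time as the model terms. If siblings enrol: "analyses will be adjusted to take into account intra-sibling correlation as well". Delivery cohort does not appear.

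Under Randomization and sample size: "The sample size of 410 dyads (*n* = 205 per study arm) will be sufficient to detect a 0.3 difference between study groups". That claim concerns communication one year after the program, for a power of 90% at the 0.05 level, and it takes a control mean of 2.81 and an SD of 0.85. The same number is said to give 80% power for an 18-point difference in intention to abstain, from 50% in controls. The only adjustment listed is attrition of 10% and then 25%. There is no ICC, cohort size or design effect.

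**The concern.** Dyads are independent when randomized, but those in the intervention arm then share sessions and peers. Controls stay independent. This is a partially nested design, with clustering created by treatment in one arm.

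The shared lessons bear directly on the outcomes that set the sample size. Table 1 places communication strategies, communication styles and refusal skills, and reproductive health in group lessons. If some cohorts respond better than others, cohort-mates' outcomes are correlated. A model without a cohort term then underestimates the variance of the intervention mean. Confidence intervals for the primary comparisons would be too narrow, and the power statement, which assumes independence, would be too high.

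**Working it through.** **Inputs from the article.** 205 dyads per arm; communication difference 0.3, SD 0.85, 90% power, significance level 0.05 with sidedness not stated; abstention 50% against 68%, 80% power; attrition 10% then 25%; cohorts of 7–12, midpoint 9.5.

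**Assumed.** Cohort ICC of 0.01 to 0.10. The article gives none.

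**Step 1: reproduce the stated sample size.**
- Retained fraction: 0.90 × 0.75 = 0.675, so 205 × 0.675 ≈ 138.4 per arm analysed.
- One-sided 0.05: n = 2 × (1.645 + 1.282)² × (0.85/0.3)² ≈ 137.5, rounded up to 138. Then 138/0.675 = 204.4, rounded up to 205. This matches.
- Two-sided 0.05: n = 2 × (1.960 + 1.282)² × (0.85/0.3)² ≈ 169. Then 169/0.675 gives 251. This does not match.

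Attrition and a one-sided test therefore account for the whole 205. Nothing is left for a design effect on communication.

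**Step 2: cohort size at analysis.** 205 dyads form about 205/12 ≈ 17 to 205/7 ≈ 29 cohorts, or about 22 at 9.5 each. If attrition is spread over cohorts, the matching size among the 138 analysed is m = 9.5 × 0.675 ≈ 6.4. Keeping m = 9.5 with 138 analysed means about 138/9.5 ≈ 15 cohorts, that is, whole cohorts lost. It serves as an upper case.

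**Step 3: variance.** Intervention-arm design effect DE = 1 + (m − 1) × ICC; control arm 1. The inflation of the variance of the difference is V = (1 + DE)/2.

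**Step 4: consequences.**
- Two-sided type I error when cohorts are ignored = 2 × [1 − Φ(1.96/√V)].
- Communication power, one-sided = Φ(0.3/(0.85 × √((1 + DE)/138.4)) − 1.645).

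Example at ICC 0.05, m = 6.4: DE = 1.271, V = 1.135. Type I error: 1.96/√1.135 = 1.84, giving 6.6%. Power: 4.152/√2.271 − 1.645 = 1.11, giving 86.7%.

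| ICC | V (m = 6.4) | Type I error (m = 6.4) | Communication power, one-sided (m = 6.4) | Type I error (m = 9.5) |
|---|---|---|---|---|
| 0 | 1.000 | 5.0% | 90.2% | 5.0% |
| 0.01 | 1.027 | 5.3% | 89.5% | 5.5% |
| 0.02 | 1.054 | 5.6% | 88.8% | 6.0% |
| 0.05 | 1.135 | 6.6% | 86.7% | 7.5% |
| 0.10 | 1.271 | 8.2% | 83.1% | 10.1% |

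**Step 5: intention to abstain.** With 138.4 per arm, 50% against 68% and a two-sided 0.05 test, power before clustering is 86.5%. Applying DE to the intervention-arm variance only, power falls to 80% at these ICCs:

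| Enrolled cohort size | No shrinkage | After attrition (× 0.675) |
|---|---|---|
| 7 | 0.066 | 0.106 |
| 9.5 | 0.046 | 0.073 |
| 12 | 0.036 | 0.055 |

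**The case against.** **The harm is conditional.** A reader might infer that the standard errors are too small and that type I error exceeds 5%. The article does not support that as fact, because it gives no ICC. Dyads are randomized individually, so similarity that exists before randomization does not bias the comparison. If the program affected nobody, the ordinary test would hold about 5%. Inflation needs cohorts that respond differently around an average effect of zero. This stands, and it makes the point conditional.

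**Shared facilitators add little.** Each site has two family health coaches, and group lessons are taught by two. With that staffing, the facilitator effect in group lessons is largely a site effect, and site is the stratification factor. What remains is mainly peer interaction in five of 11 lessons, with the power statement set at 12 months. This stands. It argues against assuming a high ICC but does not show that the ICC is zero.

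**Communication power in the seventies.** Combining clustering with a two-sided test gives about 76% to 79% at ICC 0.05. That mixes two issues: with a two-sided test, power is already about 83.5% before any clustering. Only the fall from 90% in the table is due to cohorts.

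**Left to the analysis plan.** Random-effects detail often sits there, and that plan is not shown. However, the article does name its model terms, the correlations it handles and the assumptions behind its power, and cohort is in none of them. Reading the within-group correlation as cohort correlation is strained, since the sentence ties it to longitudinal data.

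**Conclusion.** The point holds in a conditional form. The intervention arm is clustered by delivery and the control arm is not, while the stated model and sample size treat cohort-mates as independent. Given a positive cohort ICC, the direction is certain: the standard error is understated and communication power is below the stated 90%.

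The size is modest at low ICC and material at higher values. Across ICC 0.01 to 0.10, two-sided type I error runs from about 5.3% to 8.2% at 6.4 dyads per cohort, and from 5.5% to 10.1% if retained cohorts stay at 9.5. Communication power, on the one-sided basis that the 205 implies, runs from about 89% to 83% at 6.4 per cohort.

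A reader might extend the power criticism to both sample-size outcomes. That is not supported: intention to abstain keeps at least its stated 80% until the ICC passes roughly 0.04 to 0.10, depending on cohort size. Its standard error would still be understated.

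These figures rest on the assumed ICC range, equal cohort sizes and a normal approximation.

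**What to change.** - Record the delivery cohort of each intervention dyad. The article does not say that this is captured.
- In the primary mixed model, add a random effect for delivery cohort in the intervention arm only, with each control dyad as its own cluster. Use small-sample degrees of freedom, as there are only about 17 to 29 cohorts. For the binary outcome, a cluster-robust equivalent would serve.
- Include site, the stratification factor, in the model.
- Describe the initial t-tests and chi-square tests as descriptive. They may stay, but conclusions should rest on the model.
- Restate communication power over an assumed ICC range of 0.01 to 0.10, giving the cohort size used and whether the test is one- or two-sided.

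The cost is one recorded variable, changed analysis wording, slightly wider confidence intervals and a lower stated power. No added participants or assessments are needed. The change should be made before outcome data are examined; the Data management section provides for an analysis part way through the trial, so settling the model beforehand avoids a choice made with results in view.
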